## Abstract

**Background:**

About one third of breast cancer survivors suffer from persistent severe fatigue after completion of curative cancer treatment. Face-to-face cognitive behavioral therapy (F2F CBT), especially designed for fatigue in cancer survivors, was found effective in reducing fatigue. However, this intervention is intensive and treatment capacity is limited. To extend treatment options, a web-based version of CBT requiring less therapist time was developed. This intervention is aimed at changing fatigue-perpetuating cognitions and behaviors. The efficacy of web-based CBT will be examined in a multicenter randomized controlled trial.

**Methods:**

In total, 132 severely fatigued breast cancer survivors will be recruited and randomized to either an intervention condition or care as usual (ratio 1:1). Participants will be assessed at baseline and 6 months thereafter. The intervention group will receive web-based CBT, consisting of three F2F sessions and maximally eight web-based modules over a period of 6 months. The care as usual group will be on a waiting list for regular F2F CBT. The total duration of the waiting list is 6 months. The primary outcome of the study is fatigue severity. Secondary outcomes are functional impairments, psychological distress and quality of life.

**Discussion:**

If web-based CBT is effective, it will provide an additional treatment option for fatigue in breast cancer survivors. Web-based CBT is expected to be less time-consuming for therapists than regular F2F CBT, which would result in an increased treatment capacity. Moreover, the intervention would become more easily accessible for a larger number of patients, and patients can save travel time and costs.

**Trial registration:**

Dutch Trial Registry - NTR4309

**Electronic supplementary material:**

The online version of this article (doi:10.1186/s12885-015-1787-7) contains supplementary material, which is available to authorized users.

## Background

Worldwide, breast cancer is the most common malignancy in women. About 1.7 million new cases were diagnosed in 2012 [1]. In the last decades, survival rates have been improved due to early detection by screening programs and advances in oncological treatments [2, 3]. Since the number of breast cancer survivors increases, concerns are raised about their long-term well-being. After completion of curative cancer treatment, side-effects can become chronic. One of these persistent side-effects is cancer-related fatigue [3]. The National Comprehensive Cancer Network defined cancer-related fatigue as “a distressing, persistent, subjective sense of physical, emotional and/or cognitive tiredness, related to cancer or cancer treatment, that is not proportional to recent activity and interferes with usual functioning” [4]. Once the malignancy is successfully treated, the fatigue is expected to decrease. Nevertheless, severe fatigue becomes a chronic condition in approximately one-third of breast cancer survivors [5–8].

### Interventions for fatigue in cancer survivors

Since persisting severe fatigue interferes with daily functioning and has profound effects on quality of life, it should not be left untreated [5, 9]. The evidence of available interventions was recently evaluated in a practice guideline of the American Society of Clinical Oncology [10]. It was concluded that there is evidence for the efficacy of physical and psychosocial interventions. Initiating or maintaining adequate levels of physical activity [11–19], (cognitive) behavioral therapy [20–25], and (psycho) educational interventions [20, 25, 26] can reduce fatigue. In addition, there is some evidence for the efficacy of mindfulness-based approaches [21, 27, 28], yoga [29, 30], and acupuncture [31, 32].

The current study focuses on one of these evidence-based interventions: cognitive behavioral therapy (CBT). A CBT protocol for fatigue in cancer survivors with various tumor types was developed and tested in a randomized controlled trial (RCT) at our treatment center, the Expert Center for Chronic Fatigue of the Radboud university medical center (Radboudumc) [22]. This RCT showed that patients reported a clinically significant reduction in fatigue and functional impairments following CBT [22]. These effects were maintained at a 2-year follow-up [33]. The efficacy of the CBT protocol was recently replicated in a RCT of Prinsen et al. [34]. The CBT protocol is based on a model of precipitating and perpetuating factors of fatigue [22]. According to this model, the malignancy and its treatment are the precipitating factors that induced fatigue. However, other factors are responsible for the persistence of severe fatigue after cancer treatment [22]. These fatigue-perpetuating factors and the overall explanatory model are captured in Fig. 1. Each fatigue-perpetuating factor is addressed in a module of the CBT protocol, offered as regular face-to-face (F2F) therapy. However, this F2F CBT is intensive for both therapists and patients, since it consists of 12 to 14 F2F sessions over a period of 6 months. Therapists need to invest considerable time to deliver these sessions and a limited number of trained cognitive behavioral therapists provide this F2F therapy. Besides, patients need to travel to a treatment center to attend the sessions. The development of web-based CBT would reduce the therapist time needed to deliver the intervention and increase treatment accessibility for severely fatigued breast cancer survivors.

**Fig. 1 Fig1:**
[figure not shown]
Explanatory model of the CBT protocol

### Web-based CBT

The fast-growing field of e-health has created new possibilities in the development of web-based interventions. Web-based CBT has been developed and examined for a wide range of mental health problems, and so far, results are promising. Multiple studies have shown that web-based CBT can be effective in reducing mental health problems [35]. To extend treatment options for severely fatigued breast cancer survivors, we have developed a web-based version of our F2F CBT protocol for severely fatigued cancer survivors, named “On the road to recovery”*.* The efficacy of this intervention will be examined in a RCT, named “the CHANGE-study”.

### The right time to intervene

In our previous RCT’s examining regular F2F CBT for severely fatigued cancer survivors, the intervention was offered at least 1 year after completion of cancer treatment [22, 34]. However, recent research has shown that the level of fatigue does not decrease further after 3 months following curative cancer treatment [36], and fatigue-perpetuating factors can already be identified at 3 months following cancer treatment [37]. Therefore, it might be possible to treat fatigue in cancer survivors at an earlier stage. To examine if this is the case, the web-based CBT will be offered at least 3 months after completion of cancer treatment.

### Aims of the CHANGE study

To examine the efficacy of web-based CBT for severely fatigued breast cancer survivors on fatigue severity compared to care as usual.To examine the efficacy of web-based CBT for severely fatigued breast cancer survivors on functional impairments, psychological distress, and quality of life compared to care as usual.To examine if time since completion of cancer treatment moderates the efficacy of web-based CBT with respect to fatigue severity.

## Methods

The method section of this study protocol is written in accordance with the CONSORT statement for reporting parallel group randomized trials [38] and the CONSORT e-health criteria for reporting web-based interventions [39].

### Design

A non-blinded multicenter RCT (the CHANGE-study) will be conducted to evaluate the efficacy of web-based CBT compared to care as usual for severely fatigued breast cancer survivors.

### Recruitment

#### Referrals by medical professionals

Patients will be recruited by medical professionals (physicians and nurses) at the outpatient clinic of the departments of surgery and/or oncology of eight hospitals in the Netherlands (Radboudumc, Nijmegen; Canisius Wilhelmina hospital, Nijmegen; hospital Gelderse Vallei, Ede; hospital Bernhoven, Uden; hospital Pantein, Boxmeer; VieCuri medical center, Venlo; Elkerliek hospital, Helmond; Slingeland hospital, Doetinchem). Physicians and nurses will inform eligible patients about the study during regular medical follow-up consults and give them an information leaflet. If a patient agrees to be informed about the study by the researcher, the nurse practitioner will fill out a participation form and send it to the researcher (HA). Subsequently, the researcher will call the patient to give a detailed explanation about the study and to address questions.

As a second recruitment strategy, nurse practitioners from selected participating hospitals will identify cohorts of eligible patients through medical records. They will inform these cohorts about the CHANGE-study by mail. Patients will receive an information leaflet with an accompanying letter. In this letter, patients are asked to contact the researcher if they want to participate in the study.

#### Self-referrals

Patients will also be informed about the study by leaflets and notifications on social media of patients’ associations and the Radboudumc (e.g. Facebook and Twitter). Patients can complete a participation form, integrated in an informative website. Subsequently, the researcher will contact patients by phone to inform them about the study and to address questions.

### Participants

All patients who want to participate in the study will first be screened for eligibility. The in- and exclusion criteria are shown in Table 1. To verify the medical criteria (criterion 2, 3, and 4) of self-referrals, patients will send a copy of the most recent report of their medical follow-up examination to the researcher. The researcher will administer an online screening questionnaire to verify the other criteria. All patients will sign informed consent before filling out this online screening. The Checklist Individual Strength [40] will be used to screen for severe fatigue (criterion 6). The Beck Depression Inventory for Primary Care (BDI-PC) [41, 42] will be used to screen for a depressive disorder (criterion 9). If the score on the BDI-PC is ≥4, the researcher will administer the Depression module of the Mini-International Neuropsychiatric Interview (M.I.N.I.) [43] by phone to assess the presence of a major depression. If patients meet the criteria for major depression, they will be advised to contact their general practitioner for an appropriate referral.

**Table 1 Tab1:** In- and exclusion criteria

Inclusion criteria
1) Women who are 18 years or older.
2) Treated for breast cancer with curative intent.
3) Breast cancer treatment (surgery, chemo- and/or radiotherapy) must be finished at least 3 months previously. There is no upper limit for the time since completion of cancer treatment. Patients who currently receive hormone and/or targeted therapy are eligible.
4) Disease-free at entry of the study, defined by the absence of somatic disease activity parameters.
5) Able to speak, read, and write Dutch.
6) Severely fatigued, defined by a score of ≥35 on the fatigue severity subscale of the Checklist Individual Strength.
7) Having access to a computer with internet.
Exclusion criteria
8) Presence of a co-morbidity that explains the presence of severe fatigue.
9) A depressive disorder, assessed with the BDI-PC and the M.I.N.I.
10) Current psychological treatment for a psychiatric disorder.
11) Current CBT for fatigue.

### Procedure

If patients are eligible and have signed written informed consent, they will start with a baseline assessment (T0). Following T0, participants will be randomized to either the intervention condition (web-based CBT) or the control condition (care as usual). After 6 months, all participants will be assessed again (T1). For participants assigned to the web-based CBT, this will be the post-intervention assessment. The overall study design is shown in Fig. 2. A test assistant will perform T0, T1 and the randomization.

**Fig. 2 Fig2:**
[figure not shown]
Overall study design. T0 = baseline assessment; T1 = second assessment

### Randomization

Stratified randomization will be based on time since completion of cancer treatment (3 months up to 1 year versus ≥ 1 year) and type of referral (referrals by medical professionals versus self-referrals). After T0, randomization will be performed by a test assistant in the presence of the patient. A computerized randomization tool, built by an independent statistical expert, will be used to randomly allocate patients to either intervention or control condition. The allocation ratio will be 1:1 and block-randomization will be used with a block size of six. The test assistant, the researcher and the participants will be blinded to the allocation sequence. They will not be blinded for the randomization outcome, because this is not possible in psychological treatments.

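### One published, fixed block size of six in an open trial could let up to about a quarter of allocations be known in advance; varying, undisclosed block sizes are a cheap improvement

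*Protocol article*

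**What the plan says.** The Randomization section of the protocol article sets out a computerised tool built by an independent statistical expert. It states that "The allocation ratio will be 1:1" and that "block-randomization will be used with a block size of six". There are two binary stratifiers, time since the end of cancer treatment (under or at least one year) and referral route (medical professional or self-referral), so there are four strata. Hospital is not a stratum.

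On masking, the section says "The test assistant, the researcher and the participants will be blinded to the allocation sequence", and then of the same people: "They will not be blinded for the randomization outcome". The Design section calls the trial non-blinded.

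The roles are divided. Under Participants, "The researcher will administer an online screening questionnaire to verify the other criteria"; the researcher also gives the telephone depression interview. Under Procedure, "A test assistant will perform T0, T1 and the randomization". Randomisation follows eligibility, consent and the baseline assessment, with the patient present.

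**The concern.** Blinding staff to the list conceals the next allocation only if it cannot be inferred from earlier ones. Here the earlier allocations are visible, the block size is a single stated number, and both stratifiers are known before a patient is randomised. Within a stratum, once three patients in a block have gone to one arm, the rest of that block is determined.

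A tally is practicable. Allocations from all eight hospitals feed only four lists. According to the Recruitment section, both medically referred patients and self-referrals pass through the researcher by telephone.

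What is at stake is selection bias. A screener who knows the next arm could, even unintentionally, be stricter or more lenient with a borderline patient, or shift the date of the baseline visit. The criterion on comorbidity that explains the fatigue (Table 1) is a judgement with no stated threshold, and the Development section lists the researcher among the authors of the intervention's content. The primary outcome is self-reported in an open comparison with a waiting list, so concealment before allocation is one of the few protections against bias that this design can offer.

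**Working it through.** **Inputs.** Block size 6, ratio 1:1 and four strata (Randomization); total sample 132 (Power). The article gives no predictability figure. Its sample size reproduces: 60 × 0.87 = 52.2, rounded up to 53; 53 / (1 − 0.195) = 65.8, rounded up to 66 per arm; 2 × 66 = 132.

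**Step 1: certain allocations in a complete block.** A 3:3 block has C(6,3) = 20 equally likely orderings. An assignment is certain when one arm has used its three places.
- Positions 1 to 3: never.
- Position 4: 2 of 20 orderings = 0.10.
- Position 5: 8 of 20 = 0.40.
- Position 6: 20 of 20 = 1.00.

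The sum is 1.5 of 6, or 25%. The closed form for a block of 2m, 2m/(m + 1), gives 6/4 = 1.5 for m = 3.

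**Step 2: best guess.** Always guessing the arm with more places left is right with probability 0.5, 0.6, 0.6, 0.7, 0.7 and 1.0 at positions 1 to 6. That sums to 4.1 of 6, or 68.3%, against 50% with no information.

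**Step 3: over the whole trial.** With complete blocks only, 132/6 = 22 blocks × 1.5 = 33 patients. The last block in each stratum will usually be incomplete. For 0 to 5 patients in it, the expected number of certain allocations is 0, 0, 0, 0, 0.1 and 0.5 (mean 0.1), whereas 25% of those patients would be 0.625 on average. The shortfall is 0.525 per stratum, or 2.1 over four strata. So 33 − 2.1 = 30.9 patients, and 30.9/132 = 23.4%. Simulating three different splits of patients across the strata gave 30.9 each time.

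**Step 4: when other patients are pending.** Steps 1 to 3 assume the observer has seen every earlier allocation in the stratum. If some are not yet made when the decision is taken, enumerating the same 20 orderings gives:

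| Unseen allocations ahead of the patient | Certain | Best guess right |
|---|---|---|
| 0 | 25% | 68% |
| 1 | 8.3% | 60% |
| 2 | 1.7% | 57% |

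With one unseen, for example, the certain cases are 0.10 (position 5) + 0.40 (position 6) = 0.5 of 6.

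**Step 5: effect of varying the block size.** Simulation with 33 patients per stratum (132/4) and an observer who knows the possible sizes and all past allocations:

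| Block sizes | Certain | Best guess right |
|---|---|---|
| 6 only | 23% | 67% |
| 4, 6 | 6% | 69% |
| 4, 6, 8 | 2 to 3% | 67% |
| 2, 4, 6 | 4% | 69 to 70% |

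Varying the sizes removes most of the certainty but hardly changes the guessing rate. Including blocks of 2 gives the highest guessing rate of the four.

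**The case against.** Much of the case on the other side stands.

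- **Roles.** A reader might infer that the same staff screen and randomise. The documents do not support this: the researcher screens, and a test assistant does the assessments and the randomisation. What holds is that both learn past allocations.
- **Upper bound.** A reader might infer that a quarter of allocations are in fact predicted. That needs someone who knows the block size, tallies every stratum and has nobody pending. The article does not say that staff were told the size or kept a tally.
- **Timing.** Eligibility is settled before the baseline assessment. The actometer and sleep diary in Table 2 run for 12 days, so patients may well be pending when the researcher decides. How many is not stated, so the figures in the second and third rows of the pending-patient table may be nearer the truth than the first.
- **Limited discretion.** Fatigue is a questionnaire score with a cut-off, the depression interview is a structured instrument triggered by a score, and self-referrals' medical criteria are checked against a report. The comorbidity criterion is the main judgement.
- **Other safeguards.** It would be too strong to say that nothing later protects against selection. The primary ANCOVA adjusts for baseline fatigue, which partly covers selection on baseline severity, though not on unmeasured prognosis.
- **No contradiction.** The Randomization section claims blinding to the sequence only and says openly that outcomes are not blinded.

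None of this removes the core point: with visible outcomes and one disclosed block size, blinding to the list does not by itself conceal the end of each block.

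**Conclusion.** The point holds as a cheap improvement to a design choice, not as an error or as evidence of bias. With a fixed block of six and visible past allocations, up to 25% of assignments per complete block, about 31 of 132 patients (23%) over the trial, could be known with certainty beforehand. That bound assumes a known block size, a complete tally in each of the four strata and no other patient pending in the stratum. With one or two pending it drops to 8.3% or 1.7%. Whether anyone could or did make use of it cannot be told from the article. The 68% guessing rate should not be put forward as a harm that the remedy cures, because varying the block sizes leaves it almost unchanged.

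**What to change.** For all remaining randomisations, have the independent statistical expert set the tool to draw block sizes at random within each stratum, for example 4, 6 and 8, avoiding blocks of 2. The sizes should be known only to that expert and withheld from recruiting staff until enrolment closes. Publication of the original size cannot be undone, but it no longer helps once the sizes change.

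The cost is a settings change in an existing tool; sample size and analysis stay as they are. The downside is a slightly larger possible imbalance: the most one stratum can be out of balance at any moment rises from 3 patients (half of 6) to 4 (half of 8).

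If enrolment has already finished, report who knew the block size during recruitment, and compare baseline characteristics of patients in positions that were certain with those of the rest.

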### Intervention

#### Development

*On the road to recovery* is built in a web portal, designed with technical guidance from the Psychological and Psychiatric Care Innovation (Utrecht, The Netherlands) [44]. Experts in the field of fatigue in cancer survivors developed the content of this web portal. Trained, experienced cognitive behavioral therapists (HK, TB) and researchers (MGI, HA) wrote the texts and assignments. In total, the web portal consists of 13 texts and 26 assignments. A graphic designer developed the lay-out of *On the road to recovery*, and a videographer made 13 videos together with a therapist (HK) and the researcher (HA). These videos are integrated in the web portal. In the first video, a medical oncologist (SV) explains the rationale of the CBT. The other 12 videos are interviews of three cancer survivors. These patients are recovered from fatigue after receiving F2F CBT, and tell about their experiences with the CBT modules. A screenshot of the web portal is provided in Fig. 3. For this occasion, the text is translated into English.

**Fig. 3 Fig3:**
[figure not shown]
Screenshot of *On the road to recovery*

#### Usability testing

Five severely fatigued breast cancer survivors, who were following F2F CBT, participated in a test pilot. The usability of the web portal was tested by using a “think aloud procedure” [45]. Participants were asked to think aloud while independently completing the modules. In the meanwhile, the researcher (HA) noted obstacles they encountered (i.e. usability problems and problems with text readability). Afterwards, all participants filled out a feedback form. They were asked about the sufficiency of information provided, text readability, and the lay-out and usability of the web portal. The findings of the usability testing were used to optimize the final version of the web portal.

#### Intervention condition: on the road to recovery

All participants in the intervention condition will follow *On the road to recovery,* a web-based version of the regular F2F CBT for severely fatigued cancer survivors. Participants will start with two F2F sessions with their therapist. In these sessions, the CBT model for fatigue in cancer survivors (Fig. 1) will be explained and a treatment plan will be made. Thereafter, participants will follow *On the road to recovery* online. The web-based CBT consists of eight treatment modules. All participants will start with setting their treatment goals *(module 1)*. Then, they will work on the fatigue-perpetuating factors that are applicable to them: (1) poor coping with breast cancer and breast cancer treatment; (2) high fear of cancer recurrence; (3) dysfunctional fatigue-related cognitions; (4) a deregulated sleep-wake rhythm; (5) a deregulated activity pattern; and/or (6) negative social interactions and low social support. Each of these six fatigue-perpetuating factors coincides with a treatment module *(module 2–7)*. At baseline assessment, it is decided which modules are relevant for each participant. Finally, all participants will complete the therapy by realizing their treatment goals *(module 8). On the road to recovery* is tailor-made. Assessment tools are used to assess which fatigue-perpetuating factors are present and to determine which treatment modules patients need to follow (Table 2). All treatment modules consist of three parts: psycho-education (“READING”), assignments in which participants work on fatigue-perpetuating factors (“DOING”) and a final assignment, in which participants evaluate their progress (“REVIEW”). The content of the eight treatment modules is described in more detail in Additional file 1.

**Table 2 Tab2:** Tools to assess which treatment modules are indicated

Treatment module	Instrument [REF]	Outcome	Response format	Psychometric properties	Cut-off value
1. Coping with cancer and cancer treatment	Impact of Event Scale [62]	Intrusion and avoidance	4-point Likert scale, range 0–60	Cronbach’s α ranges between 0.87 and 0.96; adequate convergent validity [63]	Score ≥10 for each separate scale
2. Fear of cancer recurrence	Modified cancer acceptance scale [53]	Fear of disease recurrence	4-point Likert scale, range 3–12	N/A	Score ≥7
	Cancer worry scale [64]	Worries about the risk of developing cancer (again)	4-point Likert scale, range 8–32	Cronbach’s α = 0.87; good convergent and divergent validity [64]	Score ≥14 [64]
3. Helpful thinking	Modified causal attribution list [52, 65]	Somatic and non-somatic attributions	4-point Likert scale	Cronbach’s α ranges between 0.71 and 0.77 [65]	N/A
	Illness management questionnaire [65–67]	Focusing on symptoms	6-point Likert-scale, range 9–54	Cronbach’s α ranges between 0.85 and 0.93 [66]	Score ≥30
	Fatigue catastrophizing scale [68]	Catastrophizing in response to fatigue	5-point Likert scale, range 1–5	Cronbach’s α = 0.85 [68]	Score ≥2 (magnifying); score ≥7 (ruminating).
	Self-efficacy scale [33, 65]	Self-efficacy with respect to fatigue	4 point Likert scale, range 7–28	N/A	Score ≤19
4. Sleep-wake rhythm	Sleep-wake diary	Sleep-wake rhythm	Bedtimes and wake-up times of 12 consecutive days and nights	N/A	N/A
5. Activity regulation	An actometer, a motion-sensing device, worn to the ankle for 12 consecutive days and nights	Activity pattern (relatively active versus low active)	Average physical activity level (number of accelerations per 5 min period) [69]	Adequate reliability and validity [73]	N/A
6. Social support	Van Sonderen Social Support Inventory, subscales Interactions (SSLI) and Discrepancies (SSLD) [70]	Discrepancy between actual and desired social support	4-point Likert Scale, range 34–136	Cronbach’s α = 0.93 (SSLI); α = 0.95 (SSLD); good content validity [71]	Score ≥14 (SSLI); score ≥50 (SSLD)

Therapists will contact patients two-weekly by e-mail to give feedback on their progress and to answer questions. Therapists can also initiate video sessions with a secured video consultation system (Facetalk) [46]. These video sessions are in particular recommended for the modules “Fear of cancer recurrence” and “Coping with cancer and cancer treatment”. The guideline is to plan maximally two video sessions. The maximum duration of *On the road to recovery* is 6 months. Therapists will be blinded for the level of fatigue severity (primary outcome measure). Only after the post-treatment assessment (T1), they will be informed about the levels of fatigue severity on T0 and T1. The outcomes with respect to fatigue severity and other disabilities will be discussed with the participant in a final F2F session. In this session, the therapist and patient will determine if the patient is recovered from severe fatigue. If patients are not recovered from severe fatigue, F2F therapy will be offered outside the study context.

